## Abstract

**Background:**

Adolescent insomnia is a prevalent issue with significant implications for mental and physical well-being. Given the increasing incidence of sleep disorders, there is an urgent need for safe and efficient treatment modalities, particularly non-pharmacological interventions. Auricular point therapy, a prominent element of acupuncture in China, is often employed to address insomnia. However, there remains a lack of research on the efficacy of auricular point-vagus nerve stimulation in managing insomnia among teenagers. To evaluate the efficacy of this interventions and explore the regulatory mechanisms of brain function, a randomized trial is planned.

**Methods/design:**

This trial is a single-center, single-blind, randomized controlled study. A total of 174 adolescent patients with insomnia will be randomly assigned to either the treatment or control groups. Over a period of 4 weeks, patients in the experimental group will undergo bilateral auricular point-vagus nerve stimulation, while those in the control group will receive bilateral non-auricular acupoint-vagus nerve stimulation. Data collection will occur at baseline, 1 week into the intervention, 4 weeks post-treatment initiation, and 4 weeks post-treatment completion. The primary outcome measures will include the Pittsburgh Sleep Quality Index (PSQI), Adolescent Sleep Hygiene Habits Scale (ASHS), and Adolescent Sleep Assessment Questionnaire (DSM). Secondary outcome measures encompass the Self-Assessment Scale for Anxiety (SAS), Self-Depression Scale (SDS), Quality of Life Scale (SF-36), and Autonomic Composite Score (COMPASS-31). Other indicators will involve the use of functional magnetic resonance imaging (fMRI), heart rate variability (HRV), and polysomnography (PSG).

**Discussion:**

The findings of this study will provide strong support for the use of auricular-vagus nerve stimulation as a safe and effective non-pharmacological intervention for insomnia. This approach will offer advantages over medication by mitigating the risks of addiction and adverse effects associated with prolonged drug therapy. Furthermore, the results will align with prior research that underscores the positive impact of auricular acupuncture point stimulation on enhancing sleep quality.

**Clinical trial registration:**

https://www.chictr.org.cn, ChiCTR2400087889.

## Introduction

1

Sleep is a critical physiological necessity for humans and plays a pivotal role in both physical and mental well-being. The increasing prevalence of sleep disturbances, notably insomnia, among adolescents in recent years significantly affects teenagers’ educational attainment and quality of life (1). Studies have reported varying rates of insomnia among Chinese adolescents, ranging from 19.3 to 38.2%, showing a gradual increase over time (2, 3). A meta-analysis of sleep patterns worldwide among 11–18-year-olds revealed that adolescents frequently experience sleep quality problems such insomnia and trouble falling asleep in addition to sleep deprivation (4). Beyond its impact on daytime functioning, insomnia is closely associated with psychological challenges such as depression and self-harming tendencies (5, 6). Hence, there is a pressing need in public health to explore effective interventions for adolescent insomnia.

Based on their pharmacodynamic effects, the medications currently employed for treating insomnia are primarily categorized into four groups: benzodiazepine receptor agonists, melatonin receptor agonists, histamine receptor antagonists, and orexin receptor antagonists (7). Despite their rapid onset of action, prolonged utilization can result in addiction, drug resistance, and various adverse health effects, particularly in teenagers (8). Non-pharmacological interventions represent a substantial progression in the quest for treatment that are less detrimental and more acceptable to this age group.

Excessive autonomic nervous system activity, elevated neurogenic inflammatory factors, and heightened sensitivity to various stimuli are key contributors to insomnia (9, 10). Strong correlations exist between vagus nerve activity and sleep quality (11). Vagus nerve stimulation can directly modulate autonomic nervous system balance, activate the body’s cholinergic neuron system, and reduce inflammatory mediator release (12), making it an effective insomnia treatment. However, surgical risks, postoperative complications, and high device revision rates have limited the widespread adoption of implantable vagus nerve stimulation (13). Auricular point-vagus nerve stimulation offers a non-invasive alternative, circumventing these concerns. The auricular branch of the vagus nerve is distributed across the inner half of the ear, the only superficial vagal projection area on the body (14). Key acupoints in this region, such as *Heart*, *Spleen*, *Liver*, *Kidney*, *Shenmen*, and *Sympathetic* are frequently used in insomnia treatment. The external auricular concha, with its thin and highly sensitive skin, is the optimal surface site for non-invasive vagus nerve stimulation and has shown notable clinical efficacy in adult patients (15).

While some studies suggest that auricular vagus nerve stimulation may increase cortical arousal and alertness, potentially counteracting its benefits for insomnia (16). Others indicate that these effects depend on stimulation intensity and frequency. Low-intensity, low-frequency stimulation produces only transient arousal, whereas repeated vagus nerve stimulation enhances parasympathetic tone, ultimately promoting sleep (17, 18). Given the complexity of auricular vagus nerve stimulation and the lack of clarity regarding its efficacy in adolescents with insomnia, this study aimed to investigate the neurological processes involved in auricular vagus nerve stimulation and assess its therapeutic potential for teenage insomnia.

## Methods and analysis

2

### Study design

2.1

On August 6, 2024, the study was registered in the Chinese Clinical Trial Registry.^1^ This research is a randomized controlled prospective single-blind clinical trial. A total of 174 participants were sought in Zhejiang Province. The dynamic randomization method of a central randomization system was used to randomly group the subjects who met the inclusion criteria. The placebo group is selected as the control group. Electroacupuncture will be used to stimulate bilateral auricular point-vagus nerve locations in the treatment group and bilateral non-auricular-vagus distribution areas in the control group. The evaluation of therapeutic indicators is carried out by personnel who are unaware of the grouping situation, and the separation of researchers, operators, and statisticians is implemented. The 8-week trial is divided into 4 weeks of therapy and 4 weeks of follow-up. The Chinese Guidelines for the Diagnosis and Treatment of Insomnia Disorders, which were compiled by the Chinese Sleep Research Society in 2019, provided the relevant criteria used to develop the study protocol (No.1.0, Date: 2024.01.15). Further details are provided in Figures 1, 2.

**Figure 1 fig1:**
[figure not shown]
SPIRIT schedule.

**Figure 2 fig2:**
[figure not shown]
Trial flow chart.

### Study setting

2.2

The study is conducted at Third Affiliated Hospital of Zhejiang Chinese Medical University, which leads the group and provides the medical resources and expert staff required to support the project’s execution. The Department of Acupuncture and Moxibustion, which has skilled medical personnel and cutting-edge therapeutic equipment suitable for undertaking the study of auricular-vagus nerve stimulation therapy, hosts the investigation. The intervention is administered to participants in a hospital treatment room that has been reserved. To ensure the safety and effectiveness of the therapy, the treatment room is equipped with the necessary electroacupuncture and monitoring equipment. The hospital creates a calm, cozy environment that encourages participant relaxation and minimizes the impact of external factors on the treatment’s efficacy. The humidity, light, and temperature of the treatment room is controlled to the appropriate degree.

### Ethics approval

2.3

This trial protocol had been approved by the Medical Ethics Committee of the Third Affiliated Hospital of Zhejiang University of Traditional Chinese Medicine (ZSLL-KY-2024-018-01), and registered in https://www.chictr.org.cn (Identifier: ChiCTR2400087889). This research complies with the Helsinki Declaration. Prior to the start of the study, hospital authorization had been secured. The ethics committee supervises and evaluates the design and execution of the trial procedures.

### Sample size

2.4

Non-inferiority sample size estimation for two independent samples was conducted via the Powerandsamplesize.com network. Using the PSQI score as the primary outcome, the sample size was calculated to require a minimum of 78 individuals in each group. Considering the 10% dropout rate in outpatient clinics, the sample size for each group would need to be expanded to 87, totaling 174 people. The specific calculation formula is as follows:
$$n_{A}={\mathrm{\kappa n}}_{B},n_{B}=(1+\frac{1}{\kappa }){\left(\sigma \frac{z_{1-\alpha }+z_{1-\beta }}{\mu_{A}-\mu_{B}-\delta }\right)}^{2}$$

$$1-\beta =\Phi (z-z_{1-\alpha })+\Phi (-z-z_{1-\alpha }),z=\frac{\mu_{A}-\mu_{B}-\delta }{\sigma \sqrt{\frac{1}{n_{A}}+\frac{1}{n_{B}}}}$$

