#### Hypotheses

2.10.1

After 4 weeks of treatment, the adolescents in the treatment group showed significant improvement in sleep quality compared with the control group. Including the total sleep time will increase, the time required to fall asleep will decrease, the frequency of easy awakening at night and early awakening will decrease, and the conditions of feeling sleepy, lacking energy and having difficulty concentrating in daily life will be improved and so on.

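### Section 2.4 sizes the trial with a non-inferiority formula, but the only stated hypothesis is superiority over a placebo, so the stated basis for 174 does not match the trial's question

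*Protocol article*

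**What the plan says.** Section 2.4 of the Protocol article names the method: "Non-inferiority sample size estimation for two independent samples was conducted via the Powerandsamplesize.com network". The endpoint and result follow: "Using the PSQI score as the primary outcome, the sample size was calculated to require a minimum of 78 individuals in each group". The formula printed beneath uses the one-sided quantile z(1-alpha) and has muA - muB - delta in the denominator. Alpha, power, sigma, the means and delta appear as symbols only. The allowance for dropout takes 78 to the final size: "the sample size for each group would need to be expanded to 87, totaling 174 people".

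Section 2.10.1 gives the hypothesis: "After 4 weeks of treatment, the adolescents in the treatment group showed significant improvement in sleep quality compared with the control group". Section 2.1 describes the comparator: "The placebo group is selected as the control group". Section 2.9.2 confirms a sham design, with the same instrument, process and parameters applied at a site outside the vagal distribution.

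**The concern.** A trial of active stimulation against a placebo site asks whether the active arm is better. Section 2.4 names a different test, whose usual purpose is to show that a treatment is not worse than an effective comparator by more than a margin. Being no worse than placebo would not answer the question in section 2.10.1.

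The mismatch affects what the number 78 means. In a non-inferiority calculation, part of the distance being detected is supplied by the margin, and that part adds nothing to the power to show a benefit. The same 78 can therefore go with good or poor superiority power, and the article gives the reader no way to tell which. Section 2.4 is the only justification offered for the trial's size.

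Missing inputs are not the complaint, since an article may leave those to the full protocol. The complaint is that the design label and margin term printed in section 2.4 contradict sections 2.1 and 2.10.1.

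**Working it through.** **Dropout step.** Inputs from section 2.4 are 78 per group and 10% dropout. 78 / (1 - 0.10) = 86.7, rounded up to 87, and 2 x 87 = 174. This reproduces.

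**The 78.** It cannot be reproduced, because no inputs are given. The formula can be inverted instead. With equal groups (kappa = 1), n = 2 x ((z(1-alpha) + z(1-beta)) / D)^2, where D = |muA - muB - delta| / sigma. At n = 78, D = (z(1-alpha) + z(1-beta)) x sqrt(2/78) = (z(1-alpha) + z(1-beta)) x 0.1601. The alpha and power values below are assumptions:

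- one-sided 2.5%, 80%: (1.960 + 0.842) x 0.1601 = 0.449
- one-sided 2.5%, 90%: (1.960 + 1.282) x 0.1601 = 0.519
- one-sided 5%, 80%: (1.645 + 0.842) x 0.1601 = 0.398
- one-sided 5%, 90%: (1.645 + 1.282) x 0.1601 = 0.469

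**What D implies for superiority.** Let d be the assumed true benefit in SD units. If delta = 0, then d = D. If delta is a non-inferiority margin of m SD, D = d + m, so d = D - m. If delta lies on the benefit side (superiority by a margin), D = d - m, so d = D + m.

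Two-sided 5% superiority power with 78 per arm is approximately Phi(d / 0.1601 - 1.960):

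| Assumed inputs | D | delta = 0 | a quarter of D is non-inferiority margin | half of D is non-inferiority margin |
|---|---|---|---|---|
| one-sided 2.5%, 80% | 0.449 | 80% | 56% | 29% |
| one-sided 2.5%, 90% | 0.519 | 90% | 68% | 37% |
| one-sided 5%, 80% | 0.398 | 70% | 46% | 24% |
| one-sided 5%, 90% | 0.469 | 83% | 59% | 31% |

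Two cells worked through:

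- First row, half margin: d = 0.224; 0.224 / 0.1601 - 1.960 = -0.56; Phi = 0.29.
- Third row, delta = 0: 0.398 / 0.1601 - 1.960 = 0.53; Phi = 0.70. In that case 80% power at two-sided 5% would need 100 per group.

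The opposite sign moves power up. With D = 0.40 and a superiority margin of 0.1 SD, d = 0.50 and power is about 88%.

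**What 78 evaluable per arm delivers, whatever was entered.** At two-sided 5%, 80% power corresponds to 0.449 SD and 90% to 0.519 SD. At 0.3 SD power is about 47%, and at 0.4 SD about 71%.

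**The case against.** The strongest defence is that the formula is not tied to non-inferiority. With delta = 0 it is an ordinary one-sided superiority calculation, and with delta on the benefit side it is superiority by a margin. A one-sided 2.5% quantile is the efficacy side of a two-sided 5% test, so z(1-alpha) alone is no error. On that reading the word non-inferiority could be a slip in naming, and 78 could have the intended power. This stands in part: the calculation is not shown to give the wrong number. But the article states neither reading, its label says otherwise, and no section reconciles the two.

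Two stronger readings are tempting and are not supported:

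- **That the trial is underpowered.** The low figures in the table need a particular size and sign of delta that the article does not give. The favourable cells are just as compatible with the text.
- **That the trial could declare an ineffective treatment successful by showing non-inferiority to sham.** The article proposes no such analysis. It gives no margin value and no non-inferiority decision rule, and section 2.10.1 frames success as improvement over control.

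It can also be said that section 2.5 describes recruitment as running to 31 March 2025, so a restated calculation would not be a prospective justification. That is fair. The restatement corrects the record and says what the fixed size can detect.

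**Conclusion.** The point holds as an internal contradiction. Section 2.4 attributes the sample size to a non-inferiority calculation with a margin, while sections 2.1, 2.9.2 and 2.10.1 describe a superiority comparison with a sham. As written, the stated basis for 174 does not support the trial's own hypothesis and has to be corrected.

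The effect on power cannot be given as one figure. Under the assumed settings, superiority power ranges from the full intended 80% or 90% (one-sided 2.5%, delta zero) down to between 24% and 37% (half the distance a non-inferiority margin), and it would be higher if delta lay on the benefit side. All of these rest on assumed values for alpha, power and delta. The dropout arithmetic is correct, and 78 is not shown to be too small.

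**What to change.** Rewrite section 2.4:

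- Remove the non-inferiority label and delta.
- Give a two-sided 5% superiority calculation for the between-arm PSQI difference at week 4, with the assumed difference and SD and the source of each. Choose the difference on its own grounds, not by working back from 78.
- Keep 174, and state separately what 78 evaluable per arm delivers: 80% power at about 0.45 SD and 90% at about 0.52 SD.
- State that the PSQI comparison is judged as superiority, with the two-sided 95% confidence interval for the difference excluding zero in favour of treatment (lower PSQI is better). Say that this does not change the status of ASHS and DSM, which section 2.10.2 also lists as primary.

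Adjusting for baseline PSQI by ANCOVA is an optional gain in precision. If the baseline correlation were 0.5 (an assumption), the difference detectable with 80% power would fall to 0.449 x sqrt(1 - 0.25) = 0.39 SD. The correction does not depend on it.

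The cost is one rewritten paragraph and no extra patients. The downside is that the stated power may be less favourable than the sponsor intended.

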### Participant recruitment

2.5

The recruitment period for participants ran from September 1, 2024, to March 31, 2025, following registration and ethical approval. A formal informed consent form must be signed for eligible participants to take part and the written consent of their legal guardian must be obtained.

### Diagnostic criteria

2.6

This study adopted the relevant standards stipulated in the “Guidelines for the Diagnosis and Treatment of Insomnia Disorders in China” compiled by the Chinese Sleep Research Society in 2019. Diagnostic criteria: (a) Chief complaints: inability to fall asleep, persistent inability to fall asleep, waking up earlier than intended, refusal to go to bed at the appointed hour, and inability to go asleep on one’s own without assistance from a parent or caregiver. (b) Deficits in daytime functioning: weariness or low energy; difficulty focusing, paying attention, or remembering things; impairment in social, familial, professional, or academic functioning; agitation or irritability of mood; daytime sleepiness; behavioral issues (such as hyperactivity, impulsivity, or aggression); lack of drive, energy, or motivation; vulnerability to errors or mishaps; and anxiety regarding the quality of sleep. (c) Inappropriate sleep opportunities (e.g., adequate sleep periods) or sleep surroundings (e.g., dark, quiet, safe, pleasant places) cannot account for all of these irregularities in sleep and wakefulness. (d) Chronic insomnia: >3 episodes per week for at least 3 months; unrelated to other sleep problems.

### Inclusion criteria

2.7

Patients were included if they simultaneously met all seven of the criteria: (1) Individuals who meet the diagnostic standards listed above for insomnia. (2) Age: 13–17 years old; no restrictions on gender (2). (3) A score of at least seven on the Pittsburgh Sleep Quality Index Rating Scale (PSQI). (4) Signed informed consent was obtained and obtained the written consent of their legal guardian. (5) Individuals who are able to strictly comply with the treatment requirements. (6) No major illnesses affecting the blood system, immunity, or internal organs illnesses, without any mental health issues. (7) Within 1–3 weeks, no related drugs such as benzodiazepines and melatonin were taken (based on the elimination half-life).

### Exclusion criteria

2.8

The exclusion criteria are as follows: (1) Patients who were inadvertently registered despite not meeting the eligibility requirements. (2) Patients who are under 13 years old or over 17 years old. (3) Individuals with a history of head trauma, neurological conditions, and other objective environmental causes of insomnia. (4) Individuals with severe underlying illnesses, such as endocrine, hematologic, or digestive system cancers, and patients whose conditions vagal nerve stimulation, such as hyperthyroidism and heart failure. (5) Patients with a PSQI score <7. (6) History of drug abuse or alcoholism. (7) Skin allergy, injury or inflammation at the site of auricular application. Women who are pregnant or preparing for pregnancy, or women who are breastfeeding. (8) Participation in other clinical trials in the last 6 months, or patients who have taken anticholinergic drugs or hormonal drugs in the recent past, or patients who are taking drugs to inhibit the cerebral cortex or the nervous system on an irregular basis.

### Intervention and comparison

2.9

#### Treatment group

2.9.1

The SDZ-IIB electronic acupuncture instrument (Hwato brand, Suzhou Medical Appliance Factory, China) is used for auricular point-vagus nerve stimulation. The stimulation site is the vagus nerve distribution area on both sides of the body’s ear acupuncture points, as detailed in Figures 3, 4. The treatment parameters are as follows: sparse and dense wave, 4 Hz/20 Hz, biphasic pulse with a 0.2 ms pulse width, stimulation intensity according to the patient’s tolerance level (characterized by mild tingling without discomfort). Treatment will be administered daily at noon and before bedtime for 1 h, with each treatment lasting 30 min. Treatment will be provided 5 days a week for four consecutive weeks. Patients will be trained by a medical expert to ensure that each patient or a member of their family can correctly use the device on their own and then take it home to receive treatment. Observation time points are pre-treatment baseline, 1 week into treatment, 4 weeks into treatment, and 4 weeks following the conclusion of treatment.

**Figure 3 fig3:**
[figure not shown]
Non-vagus nerve stimulate sites and vagus nerve stimulation sites.

**Figure 4 fig4:**
[figure not shown]
Treatment diagram. **(A)** Treatment apparatus; **(B)** ear clip; **(C)** treatment location.

#### Control group

2.9.2

The stimulation site is the bilateral non-auricular vagus nerve distribution area (Figure 3). The instrument, treatment process and treatment parameters are the same as those for the treatment group. Observation time points are pre-treatment baseline, 1 week into treatment, 4 weeks into treatment, and 4 weeks following the conclusion of treatment (follow-up).

### Hypotheses and outcomes

2.10

#### Hypotheses

2.10.1

After 4 weeks of treatment, the adolescents in the treatment group showed significant improvement in sleep quality compared with the control group. Including the total sleep time will increase, the time required to fall asleep will decrease, the frequency of easy awakening at night and early awakening will decrease, and the conditions of feeling sleepy, lacking energy and having difficulty concentrating in daily life will be improved and so on.

#### Primary outcome

2.10.2

In this study, the Pittsburgh Sleep Quality Index Score (PSQI), the Adolescent Sleep Hygiene Scale (ASHS), and the Adolescent Sleep Assessment Questionnaire (DSM) are used to comprehensively evaluate treatment-related changes in sleep quality. PSQI: A global measure assessing overall sleep quality through subjective sleep parameters and disturbances. ASHS: Specifically evaluates behavioral and environmental factors influencing adolescent sleep patterns. DSM: Focuses on clinical characterization of sleep disorders, including typology and severity.

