##### ASHS

2.10.2.2

The ASHS contains nine sections with scores from 1 to 6, a higher score indicates better sleep hygiene (20).

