##### DSM

2.10.2.3

The questionnaire is based on the *Diagnostic and Statistical Manual of Mental Disorders*. It can help assist in identifying sleep disorder, assess the specific manifestations and impacts of sleep problems and determine whether the treatment is effective and whether it meets the clinical criteria for symptom relief (21).

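### The protocol names three primary outcomes but sizes the trial on one, and does not say whether one, any or all must succeed

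*Protocol article*

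**What the plan says.** The protocol article settles the primary outcome in two incompatible ways.

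- **Abstract, Methods/design:** three outcomes. "The primary outcome measures will include the Pittsburgh Sleep Quality Index (PSQI), Adolescent Sleep Hygiene Habits Scale (ASHS), and Adolescent Sleep Assessment Questionnaire (DSM"). Section 2.10.2 repeats the list and says of the scales beside PSQI: "the Adolescent Sleep Hygiene Scale (ASHS), and the Adolescent Sleep Assessment Questionnaire (DSM) are used to comprehensively evaluate treatment-related changes in sleep quality".
- **Section 2.4, Sample size:** one outcome. "Using the PSQI score as the primary outcome, the sample size was calculated to require a minimum of 78 individuals in each group". Allowing for 10% dropout gives 87 per group, 174 in all.

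The scales are described as follows. PSQI (2.10.2.1) runs from 0 to 21, and higher is worse. For ASHS, section 2.10.2 says: "ASHS: Specifically evaluates behavioral and environmental factors influencing adolescent sleep patterns", and 2.10.2.2 adds: "The ASHS contains nine sections with scores from 1 to 6, a higher score indicates better sleep hygiene". For DSM, section 2.10.2 mentions both type and severity of sleep disorder, and 2.10.2.3 says it can "determine whether the treatment is effective and whether it meets the clinical criteria for symptom relief". The article gives DSM no score range or direction.

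The hypothesis (2.10.1) is better sleep quality than control after 4 weeks of treatment. It names no scale.

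**The concern.** Which outcome is primary is a protocol decision, and here it is made twice with different answers. An analysis plan cannot quietly settle it. Choosing PSQI alone would depart from the abstract and 2.10.2. Keeping all three would leave the sizing in 2.4 covering only one of them.

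The wording in 2.10.2 describes a joint purpose for the three scales, not a decision rule. Two readings stay open, with opposite costs. If a significant result on any scale counts as success, the chance of a false positive rises. If all three must be significant, power falls below whatever 2.4 aimed for. With neither excluded, a mixed result could be presented as success or failure once the data are known.

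There is also a mismatch of construct. The hypothesis predicts longer sleep, faster onset, fewer awakenings and better daytime function. ASHS, as the article describes it, rates influences on sleep rather than sleep quality itself.

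**Working it through.** **1. The plan's own figure.** 78 / (1 − 0.10) = 86.7, rounded up to 87; 2 × 87 = 174. The dropout step reproduces.

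The base of 78 cannot be reproduced, because 2.4 gives its formula in symbols only, with no values for alpha, power, SD, difference or margin. With equal groups the formula becomes n = 2 × [(z₁₋α + z₁₋β) / d]², where d is the standardised distance (μA − μB − δ)/σ. Solving for n = 78 gives d = √(2/78) × (z₁₋α + z₁₋β):

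| One-sided alpha (assumed) | Power (assumed) | Implied d |
|---|---|---|
| 0.05 | 80% | 0.398 |
| 0.05 | 90% | 0.469 |
| 0.025 | 80% | 0.449 |
| 0.025 | 90% | 0.519 |

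The remaining steps therefore use assumed error rates and show the range.

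**2. Any of three suffices.** Under independence, familywise error is 1 − (1 − α)³.
- Two-sided 5% each: 1 − 0.95³ = 0.143.
- Only false claims of benefit, 2.5% each: 1 − 0.975³ = 0.073.

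**3. All three must succeed.** There is no alpha inflation. Under independence joint power is the product: 0.80³ = 0.512 and 0.90³ = 0.729.

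**4. Allowing for correlation.** The three test statistics are taken as trivariate normal with a common correlation. The error columns were simulated with 1,000,000 draws; the power columns come from the normal distribution function.

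| Correlation (assumed) | Any-of-three error, two-sided 5% each | False claim of benefit, 2.5% each | All-of-three power, 80% each | All-of-three power, 90% each |
|---|---|---|---|---|
| 0 | 14.3% | 7.3% | 51% | 73% |
| 0.5 | 12.5% | 6.2% | 61% | 78% |
| 0.9 | 8.3% | 4.1% | 72% | 85% |

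The two error columns follow different conventions. The first is compared with 5%, the second with 2.5%.

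**5. Bonferroni at the planned size.** Power per endpoint is Φ(z₁₋α + z₁₋β − z₁₋α/₃), with one-sided α and n = 78.
- α = 0.05, 80%: Φ(1.645 + 0.842 − 2.128) = 64%
- α = 0.025, 80%: Φ(1.960 + 0.842 − 2.394) = 66%
- α = 0.05, 90%: Φ(1.645 + 1.282 − 2.128) = 79%
- α = 0.025, 90%: Φ(1.960 + 1.282 − 2.394) = 80%

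**6. Size needed to keep three primaries**, assuming the same d for each scale. Bonferroni needs 101–112 per group, or 226–250 in total after 10% dropout. All-of-three with independent endpoints needs 106–122 per group, or 236–272 in total.

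**The case against.** The strongest defence is that this is a condensed article and the analysis plan is not shown. Multiplicity methods commonly sit in the analysis plan, 2.4 does single out PSQI, and 2.10.1 does give a time point. That much stands. It does not remove the conflict, because two parts of the same document disagree on which outcome is primary.

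Four stronger readings are tempting, and the document does not support them.

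- **That the trial has no control of its error rate.** All that can be said is that none appears in this article.
- **That three scales at three visits make nine chances of success.** The abstract says "Data collection will occur at baseline, 1 week into the intervention, 4 weeks post-treatment initiation, and 4 weeks post-treatment completion", but that is a collection schedule. The hypothesis points to 4 weeks, so nine primary tests should not be counted.
- **That ASHS cannot respond, so an all-of-three rule is almost bound to fail.** The article describes no sleep-hygiene component in either arm, but it states no expected ASHS effect. That ASHS will not move is inference, and so is any power figure built on it.
- **That DSM is purely diagnostic.** The article gives it severity and a role in judging symptom relief. Its missing score range may be left to the cited source or the full protocol.

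It is also fair to say that keeping PSQI alone is not the only cure. A stated any-or-all rule, with alpha control and a new sample size, would work too.

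**Conclusion.** The point holds in this form: three primary outcomes are declared, one is sized, and this document has no rule linking them. One of the three, ASHS, is described as measuring something other than the sleep quality named in the hypothesis.

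The cost depends on which rule is meant. An any-of-three rule lets familywise error reach 8.3%–14.3% against 5%. Counting only false claims of benefit, it is about 6% to 7% against 2.5% for correlations from 0 to 0.5, and 4.1% at 0.9. An all-of-three rule leaves alpha alone but takes joint power to 51%–72% from 80% each, or 73%–85% from 90% each.

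Alpha, power, the correlations and equal standardised effects across scales are all assumptions, since the article gives none of them. The conflict itself needs none of these assumptions. It should be settled before unblinding, because a rule chosen afterwards would not be credible.

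**What to change.** Name one primary endpoint: the between-arm difference in total PSQI at week 4. Both parts come from the protocol, the scale from 2.4 and the time point from 2.10.1. Make ASHS, DSM, and PSQI at week 1 and at follow-up secondary, and align the abstract, 2.4 and 2.10.2. All scales are still collected.

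The 174 does not change on account of this point. Whether 78 per group is itself well founded is a separate question, since its inputs are not given.

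The cost is small but more than wording. ASHS and DSM lose primary status. Recruitment was dated to end on 31 March 2025, so this is a change to declared outcomes after the trial began. Section 2.12 commits the investigators to ethics review, notification and transparent disclosure of such a change, and the registry record needs updating. If three primaries are wanted instead, the protocol must state the any-or-all rule with its alpha control and re-size accordingly.
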